## Abstract

**Background:**

Current studies on salvage radiotherapy (sRT) investigate timing, dose-escalation and anti-hormonal treatment (ADT) for recurrent prostate cancer. These approaches could either be limited by radiation-related susceptibility of the anastomosis or by suspected side-effects of long-term ADT. A phase II protocol was developed to investigate the benefit and tolerability of regional hyperthermia with moderately dose-escalated radiotherapy.

**Methods:**

The study hypothesis is that radio-thermotherapy is a safe and feasible salvage treatment modality. The primary endpoint is safety measured by frequency of grade 3+ genitourinary (GU) and gastrointestinal (GI) adverse events (AE) according to Common Toxicity Criteria (CTC) version 4. Feasibility is defined by number of hyperthermia treatments (*n* ≥ 7) and feasibility of radiotherapy according to protocol. Target volume delineation is performed according to the EORTC guidelines. Radiation treatment is administered with single doses of 2 Gy 5×/week to a total dose of 70 Gy. Regional hyperthermia is given 2×/week to a total of 10 treatments.

**Results:**

European centres participate in the phase II trial using intensity modulated RT (IMRT) or volumetric modulated arc technique (VMAT). The initiating centres were participants of the SAKK 09/10 study, where the same patient criteria and target volume definition (mandatory successful performed dummy run) were applied insuring a high standardisation of the study procedures.

**Conclusions:**

The introduced phase II study implements highly precise image-guided radiotherapy and regional hyperthermia. If the phase II study is found to be safe and feasible, a multicenter phase III study is planned to test whether the addition of regional hyperthermia to dose-intensified sRT improves biochemical control.

## Background

### Salvage radiotherapy for biochemical recurrence after prostatectomy

Approximately 15–40 % of patients experience a biochemical relapse after radical prostatectomy within 5 years [1, 2]. Salvage radiotherapy (sRT) improves cancer-specific survival in these patients compared to observation alone [3]. Therefore, early salvage treatment at PSA levels below 0.5 ng/ml is recommended by European guidelines [4] to ensure a benefit for more than half the patients [5, 6]. In addition, a short prostate-specific antigen doubling time of <6 months is prognostic for metastasis suggesting only little benefit of sRT [7]. A steep sigmoidal dose–response curve was detected in the radiation dose range between 60–70 Gy. Current dose escalation from 60 to 70 Gy would increase biochemical control by approximately 20 %, indicating that dose-escalation is beneficial for these patients [6].

### Recruiting and unpublished randomized studies on salvage radiotherapy

Ongoing and/or up to now unpublished randomized studies on sRT to the prostatic fossa investigate timing [8], dose-escalation [9] and anti-hormonal treatment (ADT) [10, 11]. However, all salvage optimization studies have a risk of potentially increased morbidity, either due to radiation susceptibility of the anastomosis, or due to pharmacological side effects related to long-term ADT. The first analysis of toxicity from the dose-escalation trial comparing 64 Gy with 70 Gy demonstrated no significant differences between both dose levels with regard to GU and GI acute toxicity scored with CTCAE version 4 [12]. Therefore, further treatment intensification is reasonable and might be performed without or with acceptable increased side effects.

### Rationale for this trial

Regional hyperthermia is successfully applied as a response modifier with radiotherapy, leading to improved local control in different tumour entities including rectal cancer [13–16], gynaecologic malignancies [16–18], sarcoma [19, 20] and others. In prostate cancer, radio-thermotherapy also increased local tumour control in advanced disease with low toxicity rates [21–27]. Quality of life was not affected by regional hyperthermia [27]. According to a recently performed estimation, addition of hyperthermia to radiotherapy in prostate cancer would result in a dose-escalation equivalent to at least 10 Gy [28]. Consequently, application of regional hyperthermia could be a method to avoid radiation-based dose-escalation above 70 Gy and to circumvent ADT-related toxicity in prostate cancer patients after surgery.

There is limited experience with radio-thermotherapy as a salvage modality in prostate cancer [23] and a phase II protocol with an interim safety analysis was therefore developed. The phase II study investigates the potential benefit and tolerability of hyperthermia with moderately dose-escalated salvage radiotherapy to a total dose of 70 Gy in biochemically recurred prostate cancer after prostatectomy.

## Methods and design

### Study design

The study is designed as a multicentre prospective phase II study. An outline of the study procedures is given in Fig. 1.

**Fig. 1 Fig1:**
[figure not shown]
Design of the phase II study of radio-thermotherapy for biochemical recurrent prostate cancer

### Study hypothesis

The study hypothesis is that radio-thermotherapy is a safe and feasible salvage treatment modality.

### Primary endpoint

The primary endpoint is safety measured by frequency of grade 3+ genitourinary (GU) and gastrointestinal (GI) adverse events (AE) according to CTCAE version 4 [29]. Feasibility is defined as the number of hyperthermia treatments (*n* ≥ 7) and feasibility of radiotherapy according to protocol in ≥ 95 % of patients.

### Secondary endpoints

Quality of life (QoL) assessmentBiochemical progression-free survival defined as PSA-rise > 0.4 ng/ml or increasing PSA-level where the initial PSA-level is above 0.4 ng/ml.Clinical progression-free survival.Time without ADT, i.e., time until initiation of ADT.

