### Exclusion criteria

Patients with the following characteristics will be ineligible for this study.Persistent PSA value 4–20 weeks after radical prostatectomy > 0.4 ng/ml.Palpable mass in the prostatic fossa, unless histology proves no evidence of recurrence.Pelvic lymph node enlargement >1 cm in short axis diameter of the abdomen and pelvis (cN1), unless the enlarged lymph node is sampled and negative.Presence or history of bone metastases. Bone scan is mandatory in cases of clinical suspicion (e.g., bone pain).Other malignancies within five years before planned sRT; non-melanoma skin cancers are allowed.ADT or bilateral orchiectomy.Previous pelvic radiotherapy.Hip prosthesis.Metal clusters/markers and patients with a pacemaker.Severe or active co-morbidities impairing the feasibility of hyperthermia or dose intensified sRT including (but not exclusively limited to):chronic inflammatory bowel diseaseacute bacterial or fungal infection requiring intravenous antibiotics at the time of randomizationunstable angina pectoris and/or congestive heart failure requiring hospitalization within the last 6 monthstransmural myocardial infarction within the last 6 monthschronic obstructive pulmonary disease exacerbation or other respiratory disorders requiring hospitalization or precluding planned treatment within the study at the time of randomizationpsychiatric disorder precluding understanding of information on trial-related topics, giving informed consent or filling out QoL questionnairesConcurrent treatment with other experimental drugs or other anti-cancer therapy; treatment in a clinical trial within 30 days prior to trial entry.

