### Trial duration and follow-up assessment

The trial is planned to be initiated in summer 2015. The recruitment period of the entire study (100 patients) will take approximately 36 months. The primary endpoint of the study (acute toxicity) can be evaluated three months later. The follow-up period is three years. The whole study duration is estimated to be 75 months if the study is not terminated early (see criteria for termination). Follow-up visits are scheduled at 3 months after the end of treatment and 6-monthly thereafter, until the third year. Assessment includes overall survival, PSA-level, clinical recurrence-free survival with regard to local, regional and distant control. Time without treatment for prostate cancer and toxicity according to CTCAE 4.0 will be evaluated. QoL will be assessed at 3, 12, 24, 36 months after completion of treatment.

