The SAKK 09/10-study did not detect significant differences in CTCAE-measured acute toxicity between 64 Gy and 70 Gy. Urinary quality of life was slightly but significantly worsened in the higher dose group, independent of radiation treatment technique [12]. Reduction of the high-dose target volume in cases of clear identification of high risk areas (modified boost concept) was reasonable and was therefore introduced in this study. A first hint on efficacy of radio-thermotherapy (secondary endpoint) could allow comparison of this study with the SAKK 09/10 outcome data, since target definition, cancer-related inclusion and exclusion criteria were equal. A recently published retrospective study demonstrated a significant benefit for patients with positive margin but no macroscopic recurrence treated to at least 70 Gy compared to a patient cohort with a total dose of 66 Gy (100 % vs. 66.7 %) [42].

The RTOG 96–01 study demonstrated that sRT to 64.8 Gy and 2 years of ADT increased PSA-control (57 % vs. 40 %) without any influence on overall or disease-specific survival at 7 years [11]. However, long-term ADT is associated with general side effects such as sarcopenia, erectile dysfunction, fatigue and osteoporosis with a risk of fractures [43]. Furthermore, there are hints that changes in lipid metabolism could lead to a greater incidence of diabetes and cardiovascular disease, including renal complications [44–46]. Consequently, Ahmadi et al. concluded that the best way of preventing side effects is to only use ADT when it is absolutely indicated [43]. Cardiovascular mortality did not differ in otherwise healthy study participants of 8 randomized trials on long-term ADT [47]. However, the influence of long-term-ADT in patients with pre-existing co-morbidities remains unclear. Therefore, hyperthermia could become a sRT optimization tool to circumvent long-term ADT and its suspected side-effects.

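### Biochemical progression-free survival has PSA events only, so treatment started before the PSA limit hides failures and overstates control by an amount the protocol does not let us calculate

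*Protocol article*

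**What the plan says.** In the protocol article, Secondary endpoints, the biochemical endpoint is "progression-free survival defined as PSA-rise > 0.4 ng/ml or increasing PSA-level", with the second limb restricted to patients whose initial PSA is above 0.4 ng/ml. Both limbs are PSA criteria.

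The same list holds two further items, "Clinical progression-free survival" and "Time without ADT, i.e., time until initiation of ADT". Neither is linked to the biochemical endpoint.

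Exclusion criteria lists "ADT or bilateral orchiectomy". That concerns entry and does not govern ADT started later.

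Trial duration and follow-up assessment states "The follow-up period is three years", with visits at 3 months and then every 6 months. PSA and clinical recurrence are assessed, and "Time without treatment for prostate cancer and toxicity according to CTCAE 4.0 will be evaluated". Nothing in the article makes later treatment a biochemical event or gives a censoring rule for it.

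Results and discussion says that a first hint on efficacy "could allow comparison of this study with the SAKK 09/10 outcome data".

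**The concern.** The protocol foresees that some patients will start ADT during follow-up, since time to ADT is an endpoint. It also reports, from the RTOG 96-01 trial, that "2 years of ADT increased PSA-control (57 % vs. 40" %). So an expected post-treatment event acts directly on the variable that defines biochemical failure.

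Take a patient with initial PSA 0.3 ng/ml who starts ADT at 0.35 ng/ml because recurrence is suspected. If the PSA then falls and stays low to year 3, the literal definition records no biochemical event. That such a switch can happen below 0.4 ng/ml is plausible: for entry after prostatectomy, the protocol itself accepts two rises ending above 0.1 ng/ml, or three rises, as PSA progression.

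The error runs in one direction, towards better control. No comparison arm is described, so there is no internal contrast in which it could cancel. At stake is how far the reported biochemical control rate can be trusted as an early efficacy signal.

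**Working it through.** **The plan's own figure.** No number in the article is tied to biochemical progression-free survival. The only stated operating characteristics are those of the two-stage toxicity design, and they reproduce. Continuing with at most 9 of 50 events and rejecting H0 with at most 13 of 100, exact binomial sums give alpha = 0.0459 at a true rate of 20 % (stated: below 0.05) and power = 0.8716 at 10 % (stated: 87.2 %). None of this depends on the biochemical endpoint.

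**What each definition does with the example patient** (initial PSA 0.3, ADT at 0.35 ng/ml):

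- Biochemical endpoint as written: no event if the PSA falls.
- Time to ADT: event at ADT start.
- Clinical progression-free survival: event only if the recurrence is confirmed clinically.

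The switch is visible elsewhere, but the biochemical curve does not show it.

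**Patients with initial PSA above 0.4 ng/ml.** Any increase counts, so little room is left for ADT to pre-empt the event. The problem sits mainly with the others.

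**Illustration of size.** Two inputs are needed, and the document gives neither:

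- F, the true proportion progressing by 3 years. Assumed 30 to 50 %.
- f, the share of those progressors who start ADT or other treatment before the PSA limit. Assumed 5 to 30 %.

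I assume that every such switcher is a real failure and that the PSA then stays below the limit to year 3. Three-year control is then:

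- switch counted as an event: 1 − F
- switch ignored, no event recorded: 1 − F(1 − f), an overstatement of F × f
- censored at the switch, with proportional cause-specific hazards: (1 − F)^(1 − f)

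For F = 0.40 and f = 0.20, these are 1 − 0.40 = 0.60; 1 − 0.40 × 0.80 = 0.68; and 0.60^0.80 = 0.665.

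| F | f | Switch is an event | Censored at switch | No event recorded |
|---|---|---|---|---|
| 30 % | 5 % | 70 % | 71.3 % | 71.5 % |
| 30 % | 10 % | 70 % | 72.5 % | 73 % |
| 40 % | 20 % | 60 % | 66.5 % | 68 % |
| 50 % | 30 % | 50 % | 61.6 % | 65 % |

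Over the assumed range, the overstatement runs from 0.30 × 0.05 = 1.5 points to 0.50 × 0.30 = 15 points if no event is recorded. With censoring it runs from 71.3 − 70 = 1.3 to 61.6 − 50 = 11.6 points. Censoring shrinks the bias but does not remove it, because patients leave the risk set when failure is suspected.

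**The case against.** The best defence is that this is a one-line item in a condensed article, for an unpowered secondary endpoint. Censoring and later therapy are commonly left to the full protocol or analysis plan, and separate endpoints for PSA, clinical progression and ADT are a legitimate design that keeps early switches visible. Much of this stands. It does not remove the point, because the article states an event definition and does not merely leave one out. A plan that censored at ADT start would still overstate control, and one that counted ADT as an event would depart from the definition as printed.

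Several stronger readings are tempting and are not supported:

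- That the protocol counts early switchers as controlled. It never says so; this is the literal consequence of the definition.
- That the 17-point difference (57 − 40) measures the bias. It is the effect of adding 2 years of ADT to salvage radiotherapy in another trial at 7 years, not misclassification here.
- That the bias passes in full into a comparison with SAKK 09/10. This depends on that trial's event definition, which is not shown. If it used PSA events only, part or all of the bias could cancel.
- That the step to phase III rests on this endpoint. The article ties that step to safety and feasibility.
- That time without ADT and time without treatment for prostate cancer contradict each other. The first is a listed endpoint and the second a follow-up assessment; both can be evaluated.

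**Conclusion.** The point holds in limited form. As written, the biochemical endpoint misses failures that are treated before the PSA limit is reached, mainly in patients with initial PSA at or below 0.4 ng/ml, and censoring them would be informative. The direction of the bias is upward. Its size is unknown: roughly 1 to 15 points at 3 years, resting wholly on the assumed F, f and lasting PSA suppression. It would be near zero if few patients switch early. The consequence is confined to a secondary efficacy endpoint and possibly to its external comparison. The primary toxicity test, the 100 patients and the power are unaffected. This is a cheap improvement worth making, not a flaw that threatens the trial's main conclusion.

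**What to change.** In Secondary endpoints, define biochemical progression-free survival as the time to the first of: the PSA criterion, start of ADT or other treatment for recurrence, clinical progression, or death.

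Report a PSA-only version as a sensitivity analysis, in which PSA values after the start of ADT are not used as evidence of control. This version also serves the comparison with SAKK 09/10 if that trial used PSA-only events.

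The cost is wording only. The follow-up section already schedules PSA, clinical recurrence, survival and time without treatment to year 3, so no new visits, data or patients are needed. The downside is that the control rate becomes slightly less favourable and partly reflects when physicians start treatment; the gap between the two versions shows by how much.

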### Assessment of QoL

Quality of life (QoL) assessment using the EORTC QLQ-C30 [30], the QLQ-PR25 [31] and the Memorial Anxiety Scale for Prostate Cancer (MAX-PC) [32] questionnaires is performed at 3, 12, 24, and 36 months.

### Inclusion criteria

Patients with the following characteristics will be eligible for this study.Lymph node negative adenocarcinoma of the prostate treated with radical prostatectomy at least 12 weeks before randomization. Tumour stage pT2a-3b, R0-1, pN0 or cN0 according to the UICC TNM 2009; Gleason score available.PSA progression after prostatectomy defined as two consecutive rises with the final PSA > 0.1 ng/ml or three consecutive rises. The first value must be measured at least 4 weeks after radical prostatectomy.PSA at randomization ≤ 2 ng/ml.No evidence of macroscopic local recurrence or metastatic disease on pre-sRT-MRI (magnetic resonance imaging; with i.v. contrast) or pre-sRT-CT (multislice computed tomography with i.v. and oral contrast) of the abdomen and pelvis assessed within 16 weeks prior to randomization.WHO performance status 0–1 at randomization.Age at randomization between 18 and 80 years.Informed consent.

### Exclusion criteria

Patients with the following characteristics will be ineligible for this study.Persistent PSA value 4–20 weeks after radical prostatectomy > 0.4 ng/ml.Palpable mass in the prostatic fossa, unless histology proves no evidence of recurrence.Pelvic lymph node enlargement >1 cm in short axis diameter of the abdomen and pelvis (cN1), unless the enlarged lymph node is sampled and negative.Presence or history of bone metastases. Bone scan is mandatory in cases of clinical suspicion (e.g., bone pain).Other malignancies within five years before planned sRT; non-melanoma skin cancers are allowed.ADT or bilateral orchiectomy.Previous pelvic radiotherapy.Hip prosthesis.Metal clusters/markers and patients with a pacemaker.Severe or active co-morbidities impairing the feasibility of hyperthermia or dose intensified sRT including (but not exclusively limited to):chronic inflammatory bowel diseaseacute bacterial or fungal infection requiring intravenous antibiotics at the time of randomizationunstable angina pectoris and/or congestive heart failure requiring hospitalization within the last 6 monthstransmural myocardial infarction within the last 6 monthschronic obstructive pulmonary disease exacerbation or other respiratory disorders requiring hospitalization or precluding planned treatment within the study at the time of randomizationpsychiatric disorder precluding understanding of information on trial-related topics, giving informed consent or filling out QoL questionnairesConcurrent treatment with other experimental drugs or other anti-cancer therapy; treatment in a clinical trial within 30 days prior to trial entry.

### Radiation treatment planning

Patients will be placed in the supine position with a comfortably filled bladder and empty rectum. The use of an endorectal balloon is allowed. Target volume definition will be performed in accordance with the European organisation for research and treatment of cancer (EORTC) guidelines [33]. Organs at risk (OAR) include bladder, rectum and femoral heads. The bladder wall (BW) and rectal wall (RW) are contoured using a 5 mm internal margin. Constraints for OAR are given in Table 1.

**Table 1 Tab1:** Constraints for organs at risk (OARs) in the phase II study on radio-thermotherapy for biochemical recurrent prostate cancer

Organs at risk (OARs)	Constraints			
	V50	V60	V65	V70
Rectal wall	n.a.	≤50%	n.a.	≤20%
Bladder wall	n.a.	n.a.	≤50%	n.a.
Femoral heads	≤10%	n.a.	n.a.	n.a.

*n.a.* not applicable, *OAR* organs at risk, *V* organ volume receiving a specified dose

The definition of volumes and dose reporting will be in accordance with the International Commission on Radiation Units and Measurements (ICRU) Report 83 [34].

A modified treatment concept can be used in cases of clear identification of regions of risk (i.e., distinct localization of pT3a-region, R1-region, bed of seminal vesicles for pT3b-stages). In such cases, the standard target volume (EORTC-definition) will be treated to a total dose of 66.5 Gy (5 × 1.9 Gy/week) and the target volume for regions of risk (modified integrated boost volume) will be irradiated with 5 × 2.0 Gy/week to a total dose of 70.0 Gy.

### Salvage radiotherapy delivery

SRT is administered to a total dose of 70 Gy (35 fractions with single fractions of 2 Gy) over 7 weeks (modified treatment concept [see above] with reduced dose to the EORTC-target volume of 5x1.9 Gy/week to 66.5 Gy and an in integrated boost with 5x2.0 Gy/week to 70 Gy in regions with high risk of recurrence). SRT should be delivered once daily except at weekends. Intensity modulated RT (IMRT) or alternatively rotational techniques such as Rapidarc, Tomotherapy or volumetric modulated arc technique (VMAT) will be eligible.

### Concurrent hyperthermia

Regional hyperthermia will be carried out within 2 (max. within 4) hours after radiation treatment twice a week. Multichannel thermometry probes or MR-mapping temperature probes will be placed into the rectum and urethra/bladder and the thermal target temperature will be at least 41 °C for 60 min (maximum temperature: 43 °C). The total hyperthermia time is approximately 90 min including an induction period of 30 min. Ten hyperthermia sessions will be conducted. Hyperthermia should start in the first week of radiation treatment (see schedule in Fig. 1). Suboptimal hyperthermia sessions (time duration or temperature) are counted as hyperthermia session and will not be repeated. Due to any reason omitted hyperthermia sessions can be performed until the last fraction of radiation treatment. The interval between hyperthermia applications should be at least 48 h. Hyperthermia will be performed according to current guidelines [35, 36].

